### Study endpoints

#### Primary endpoint

The primary endpoint of this trial is the pathologic response rate according to central revision by pathology of NKI, determined after resection following neoadjuvant T-VEC and nivolumab treatment.

#### Secondary endpoints

Rate of delay of surgery > 14 days and rate of failure to perform surgery defined as no surgery at all;EFS, defined as time from randomization to any of the following events: progression of disease that precludes surgery, local or distant recurrence, or death due to any cause;Safety of neoadjuvant combination of T-VEC and nivolumab;Description of possible prognostic and predictive biomarkers, for example CD8, IFN-γ and PD-L1, and exploration of expansion of tumor-resident T cells.

#### Exploratory endpoints

Response rate according to RECIST 1.1 at week eight;Quality of life as measured by EORTC QLQ-C30 and the Melanoma Surgery Subscale of the FACT-M.

### Evaluation of efficacy

All patients included in the trial who received at least one cycle of therapy will be assessed for pathologic and radiologic response to treatment. Each patient will be assigned one of the following categories for pathologic response based on the resection specimen at week nine: pCR, near-pCR (< 10% vital tumor remaining), pathologic partial response (pPR; < 50% vital tumor remaining), pathologic non-response (pNR) or unknown (not assessable, insufficient data), according to guidelines of the International Neoadjuvant Melanoma Consortium (INMC) [28].

Furthermore, objective radiologic tumor response according to RECIST 1.1 will be measured with CT scans at baseline, week eight and every follow-up. Patients’ response will be classified as “unknown” if insufficient data were collected to allow evaluation per these criteria.

### Safety evaluation

All patients that have received at least one cycle of T-VEC + nivolumab will be evaluated for toxicity according to the National Cancer Institute’s Common Terminology Criteria for Adverse Events version 5.0 (NCI-CTCAE v.5.0) from the moment of signing informed consent until 100 days after last study treatment. Both AEs related and unrelated to treatment will be followed. Additionally, surgical complications will be scored according to the Clavien-Dindo classification [29]. Serious adverse events (SAEs) will be reported to the sponsor and the collaborating party Amgen Inc. (providing T-VEC) within 24 hours. Suspected unexpected serious adverse reactions (SUSARs) will be reported to the Central Committee on Research Involving Human Subjects (CCMO). In addition to the expedited reporting of SUSARs, the sponsor will submit an annual safety report to the CCMO and competent authority. This safety report will also be provided to the subsidising party Amgen Inc. at the time of reporting to the CCMO.

A DSMB has been instituted to monitor the safety of the patients throughout the study. Interim analyses will include only safety information and will be reviewed by the DSMB. After inclusion and treatment of every six patients a report will be provided to the DSMB with an overview of all toxicity observed up until that moment. It is intended not to include any data on response and thus not to look at the primary endpoint before the end of the study.

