**Table 2 Tab2:**
[figure not shown]
Schedule of enrollment, interventions and assessments

*And when clinically indicated. ^#^According to national/institute’s standards. ^1^Follow-up assessments according to local protocol/standard of care. Every 12 weeks (unless stated other) for up to two years after adjuvant treatment, year 3, 4, 5 according to institute’s standard. ^2^Clinical photographs will be taken of all cutaneous lesions, noting in detail the exact size and location of any (skin) lesions that exist. ^3^Hematology and chemistry. At screening, PT/INR, aPTT and serology (HIV, HbsAG, anti-HCV, HSV, anti-CMV) are also determined. ^4^Every 12 weeks during follow-up. ^5^T-VEC seroconversion dose 10^6^ PFU/mL. ^6^T-VEC dose 10^8^ PFU/mL. ^7^AEs will be graded according to CTCAE v5.0 from moment of signing informed consent. New occurring AEs and any SAEs will reported up to 100 days post last treatment. ^8^Only registration of medication that is used for treatment of immune-related AEs from moment of signing informed consent. ^9^Toxicity from prior treatment will be evaluated. ^10^100 ml heparinized blood (for PBMC). ^11^Only at week 3 prior to first nivolumab. ^12^At relapse. ^13^20 ml EDTA blood (for isolation of plasma for ctDNA). ^14^Three biopsies taken with a 14G needle of thru-cut and will be stored as fresh frozen and formalin-fixed paraffin-embedded material for translational research purposes. At baseline pathological confirmation of melanoma will be performed. ^15^If possible, surgical material should be preserved as fresh frozen and formalin-fixed paraffin-embedded material

*AE* adverse event; *aPTT* activated partial thromboplastin time; *CMV* Cytomegalovirus; *CT* computed tomography; *CTCAE* Common Terminology Criteria for Adverse Events; *ECG* electrocardiogram; *EDTA* Ethylenediaminetetraacetic acid; *HbsAG* hepatitis B virus surface antigen; *HCG* human chorionic gonadotropin; *HCV* hepatitis C virus; *HIV* human immunodeficiency virus; *HSV* herpes simplex virus; *INR* International normalization ratio; *MRI* magnetic resonance imaging; *PBMC* peripheral blood mononuclear cells; *PET* Positron Emission Tomography; *PFU* plaque-forming units; *PTT* partial thromboplastin time; *SAE* Serious Adverse Event; *WOCBP* women of childbearing potential

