The total neoadjuvant treatment duration comprises 7 weeks and is followed by surgery in week nine. The treatment schedule is based on four courses of T-VEC and three courses of nivolumab:T-VEC: Up to 4 ml T-VEC (first dose 10^6^ plaque-forming units (PFU) per mL as a seroconversion dose, subsequent doses at 10^8^ PFU per mL) in week 0, 3, 5 and 7. The volume of T-VEC to be injected into the tumor depends on the size of the tumor(s) and will be determined based on the longest diameter of each lesion according to manufacturers’ protocol [27];Nivolumab: Flatdose of 240 mg nivolumab intravenously every 2 weeks after the first intralesional T-VEC injections (starting at the second T-VEC dose at week 3, followed by the next doses at week 5 and 7).

T-VEC will be administered first, in order to achieve the best synergistic effect with influx of CD8^+^ T cells [14]. Patients will be offered adjuvant treatment as standard of care following surgery. See Fig. 1 for a full overview of the course of the trial.

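### Read literally, the toxicity analysis set leaves out a patient who receives only the week-0 T-VEC dose, although that patient counts for efficacy

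*Protocol article*

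**What the plan says.** Four places in the protocol article bear on this.

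- **Toxicity population** (Safety evaluation): "All patients that have received at least one cycle of T-VEC + nivolumab will be evaluated for toxicity". The same sentence sets the observation window, from consent to 100 days after the last study treatment.
- **Dosing schedule** (Study procedures and intervention): T-VEC is given "in week 0, 3, 5 and 7". Nivolumab follows, "starting at the second T-VEC dose at week 3, followed by the next doses at week 5 and 7". The order is deliberate: "T-VEC will be administered first, in order to achieve the best synergistic effect with influx of CD8"-positive T cells.
- **Efficacy population** (Evaluation of efficacy): here the rule reads "All patients included in the trial who received at least one cycle of therapy will be assessed" for response. No combination is required here.
- **Intended coverage** (Background, last paragraph): all 24 patients are to be assessed for both efficacy and safety.

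On data collection, a footnote to Table 2 says "AEs will be graded according to CTCAE v5.0 from moment of signing informed consent". The DSMB paragraph of Safety evaluation promises a report after every six patients treated, covering whatever toxicity has been seen so far.

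**The concern.** By design, every patient spends three weeks exposed to T-VEC alone. Someone who stops in that window, whether for an adverse event, progression or withdrawal, has received study drug but no cycle containing both drugs. Under the wording of Safety evaluation that patient is not evaluated for toxicity, yet the same patient is evaluated for response.

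It is unusual for the safety population to be narrower than the efficacy population. A safety set normally follows exposure, because a rule that requires a patient to reach a later dose can remove those who did not tolerate an earlier one. Safety is a secondary objective here, and the Discussion compares the expected toxicity with published single-agent rates. A rate that leaves out early stoppers would be a weaker basis for that comparison.

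**Working it through.** **Plan's own figure.** The article gives no figure for the toxicity population, so there is none to reproduce. The two power statements under Statistical considerations do reproduce: at least 9 of 24 responses gives 0.827 at a true rate of 0.45, and at least 22 of 24 gives 0.884 at a true rate of 0.95. Neither uses the toxicity set, so neither is affected.

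**Step 1: apply each rule to the same patient.** Take a patient who receives T-VEC at week 0 and nothing afterwards.

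| Section | Requirement | Patient counted? |
|---|---|---|
| Evaluation of efficacy | one cycle of therapy | yes |
| Safety evaluation, toxicity population | one cycle of T-VEC + nivolumab | no, read literally |
| Background | all 24 patients | yes |
| Table 2 footnote, AE grading | consent signed | yes |
| Safety evaluation, DSMB report | treated, all toxicity so far | yes |

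Only the toxicity population excludes this patient.

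**Step 2: effect on a reported rate (illustration).** Suppose 2 patients among those who received the combination have an event, and *k* further patients stop after week-0 T-VEC because of an event. The literal rule gives 2/(24 − k); all treated patients give (2 + k)/24.

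- k = 1: 2/23 = 8.7% against 3/24 = 12.5%, a difference of 3.8 percentage points
- k = 2: 2/22 = 9.1% against 4/24 = 16.7%, a difference of 7.6 points
- k = 3: 2/21 = 9.5% against 5/24 = 20.8%, a difference of 11.3 points

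The direction depends on why the patient stopped. If one patient stops without an event, the literal rule gives 2/23 = 8.7% against 2/24 = 8.3%, a slight overstatement.

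**Step 3: how likely is it that anyone is left out?** The article gives no rate of stopping before week 3, so this rests on an assumed rate *f*. The chance that at least one of 24 patients is left out is 1 − (1 − f)^24.

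- f = 0.5%: 11%
- f = 2%: 38%
- f = 5%: 71%
- f = 10%: 92%

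These values cover stopping for whatever reason *f* is taken to describe. Downward bias requires stopping with an event, which is a subset of all stopping.

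**The case against.** The strongest reply is that T-VEC + nivolumab may simply name the regimen, with the week-0 dose as its first cycle. The article does not define a cycle, its schedule speaks of courses, and starting the observation at consent fits this reading. Under it, Background, Evaluation of efficacy and Safety evaluation all agree. The reading is possible, but the article does not state it, and the efficacy section uses different words for its own population. If it is what was meant, a clarification is still needed.

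It can also be said that a condensed article leaves analysis sets to the full protocol or the analysis plan. That would answer an omission. Here a population is stated, and it is the narrower one.

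A reader might infer three stronger things, which the article does not support.

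- *That the DSMB would be misinformed.* Its report is described as covering all toxicity seen to date in treated patients, with no requirement for the combination.
- *That the adverse event data would be discarded.* Collection runs from consent, and reporting of serious adverse events and SUSARs has no combination requirement. The events would be recorded; the open question is whether they enter the toxicity evaluation.
- *That losing one patient shifts the rate by as much as the single-agent rates in the Discussion.* Those are 8% for nivolumab and 5.5% for T-VEC. The shift of 3.8 points is smaller than both.

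It is also fair to say that the exact 95% intervals for 3/24 (2.7% to 32.4%) and 2/23 (1.1% to 28.0%) overlap almost entirely, and that the Background calls the T-VEC toxicity profile mild. Both limit the practical weight of the point. Neither removes the conflict between the sections.

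**Conclusion.** The point holds as an inconsistency in a stated analysis population. Taken literally, the toxicity set excludes a patient treated with T-VEC alone, while the efficacy rule and the Background include that patient. If one such patient stopped because of toxicity, the reported rate in the illustration would fall by 3.8 percentage points, from 12.5% to 8.7%.

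This rests on the literal reading of the combination wording and on at least one patient stopping between weeks 0 and 3 with an event. The article gives no frequency for that, and it may not happen at all. T-VEC events in the first three weeks among patients who go on to nivolumab are counted in any case, because observation starts at consent. The primary test, the surgical endpoint and ongoing safety oversight are unaffected. Severity is minor to moderate.

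**What to change.** Define the safety set in one sentence as all patients who received any dose of T-VEC or nivolumab, and bring the Background, Evaluation of efficacy and Safety evaluation sections into line with it. If the week-0 dose was always meant to count as a first cycle, say so explicitly. If the full protocol or analysis plan already has an any-dose safety set, follow it and correct the sentence in the article.

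Optionally, tabulate events with onset before the first nivolumab dose separately. This keeps the profile of the combination visible without removing anyone from the denominator.

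The cost is a wording change. No additional data, patients or visits are needed, and the sample size and power statements stay as they are.

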### Evaluation of health-related quality of life

Health-related quality of life will be assessed with the European Organization for Research and Treatment of Cancer Quality of Life Questionnaire Core 30 (EORTC QLQ-C30), a self-reported questionnaire specifically developed for patients with cancer who are receiving cancer treatment and is the most common quality of life instrument used in melanoma studies [30]. The guideline of Cocks et al. [31] will be used for the interpretation of changes in QLQ-C30 scores. Additionally, the Melanoma Surgery Subscale of the FACT-M [32] will be evaluated in all patients every 12 weeks during the first year and at year two and three.

### Translational research

Tumor material (at baseline, during treatment and the resection specimen), peripheral blood mononuclear cells (PBMCs) and serum will be collected in all patients (see Fig. 1 and Table 2 for all time points) to perform in depth translational research into the mechanism of action of T-VEC in combination with nivolumab, both on the tumor and the tumor micro-environment. The planned analyses of the biopsies and PBMCs will primarily provide the information to underline our hypothesis about the synergistic effect of T-VEC and nivolumab.

### Data collection, management and monitoring

All source data from the trial will be collected and managed in the electronic case report form (eCRF) developed by the datacenter of the NKI via ALEA (FormsVision BV, Abcoude, The Netherlands), a web-based software system. The completed eCRFs must be reviewed and signed by the principal investigator or sub-investigator. The handling of personal data complies with the Dutch Personal Data Protection Act and all data management activities will follow local standard operating procedures. Statistical analysis will be performed after a database lock, after all study data have been collected and cleaned.

According to the Dutch Federation of University Medical Centers, this trial was classified as a ‘low risk’ study. This implies at least one on-site source data verification of the eCRFs and check of the Investigator Study File documents by the clinical research monitor.

### Statistical considerations

We suspect that neoadjuvant combination treatment of T-VEC with nivolumab will achieve a higher major pathologic complete response rate in patients with resectable stage IIIB/C/D-IVM1a melanoma compared to neoadjuvant treatment with either single agent T-VEC or nivolumab. Additionally, we expect that neoadjuvant T-VEC plus nivolumab will result in a higher response rate in our patient population compared to patients with unresectable disease, as the tumor burden is lower. The combination treatment will be considered successful if the major pathologic complete response rate lies significantly above the response rate of 20% obtained with neoadjuvant single agent ICI. For the current neoadjuvant combination study we thus expect a pCR (or near-pCR) rate of 45% for T-VEC combined with nivolumab. An exact binomial test with a nominal 10% two-sided significance level will have 82.7% power to detect the difference between the Null hypothesis proportion, π_0_, of 0.2 and the Alternative proportion, π_1_, of 0.45 when the sample size is 24.

Assuming a surgical success rate of 95%, defined as a complete dissection of the involved lymph nodes and/or all cutaneous/subcutaneous satellite/in-transit disease as planned, including 24 patients will have 88% power to exclude a lower level of 75% with 95% confidence (one-sided). The combination needs to be reconsidered when surgery as planned can no longer be performed due to progressive disease or AEs in more than two patients. Considering the chosen scenario of 24 patients, the study is also powered to analyze this secondary endpoint.

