Aside from the type of treatment, there is increasing evidence that the timing of the given therapies also plays a key role in the chances of a tumor response [19]. Neoadjuvant therapy, administered prior to surgery, could result in a broader tumor-specific T cell response compared to adjuvant treatment, downsizing of the tumor leading to less extensive surgery, and usage of the pathologic response for fitted (adjuvant) therapy [19, 20]. The benefit of neoadjuvant ICI has been investigated in multiple clinical trials, resulting in high pathologic complete response (pCR) rates of 25–80% [21–24]. Recently, the role of neoadjuvant T-VEC in resectable stage IIIB-IVM1a melanoma has been investigated by Dummer et al. [25] in a randomized study of single agent T-VEC followed by surgery, compared to surgery alone. This trial showed a pCR rate of 17.1% and an improved 2-year RFS and OS for the T-VEC + surgery arm (29.5% vs 16.5 and 88.9% vs 77.4% respectively).

Based on the recent data of neoadjuvant single agent nivolumab and pembrolizumab shown by Amaria et al. [23] and Huang et al. [24], with pCR rates of 25 and 20% respectively, neoadjuvant single agent T-VEC shown by Dummer et al. [25] and the abscopal effect of T-VEC in combination with ICI, we hypothesized that neoadjuvant T-VEC in combination with nivolumab can improve these pCR or pathologic near complete response (near-pCR) rates further. For this, we designed a single arm phase II trial treating patients with stage IIIB-IVM1a melanoma with resectable (sub)cutaneous satellite or in-transit metastases and/or tumor positive lymph nodes with neoadjuvant nivolumab and T-VEC (NIVEC trial). The aim of this trial is to show an improvement in pCR (or near-pCR) rate of 25% compared to the pCR rate observed by Amaria et al. [23] and Huang et al. [24], reaching a pCR rate of 45% in this patient population. In total, 24 patients will be included and evaluated for efficacy and safety. This is the first trial evaluating neoadjuvant T-VEC and ICI combination therapy and may benefit a large group of future melanoma patients.

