### Objectives

#### Primary objective

The primary objective of this trial is to investigate the major pathologic complete response rate, either pCR or near-pCR, of neoadjuvant combination of T-VEC and nivolumab, in patients with resectable stage IIIB/C/D/IVM1a melanoma, with the aim to achieve a major pathologic complete response rate of 45%.

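### The primary test sets pCR plus near-pCR against a 20% null that the article cites as a pCR-only rate, so passing it does not by itself show improvement over single-agent ICI

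*Protocol article*

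**What the plan says.** The Primary objective is to "investigate the major pathologic complete response rate, either pCR or near-pCR", with a target of 45%. Evaluation of efficacy lists pCR and "near-pCR (< 10% vital tumor remaining") as two separate categories, so the tested rate is a composite of both.

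The benchmark comes from the Background, which cites neoadjuvant single-agent nivolumab and pembrolizumab "with pCR rates of 25 and 20% respectively". The aim is then stated there as an "improvement in pCR (or near-pCR) rate of 25% compared to the pCR rate observed" in those two trials.

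Statistical considerations carries the 20% forward under a more general label. The treatment is "considered successful if the major pathologic complete response rate lies significantly above the response rate of 20% obtained with neoadjuvant single agent ICI". It adds "we thus expect a pCR (or near-pCR) rate of 45% for T-VEC combined with nivolumab" and gives an exact binomial test at a nominal two-sided 10% level, null 0.20, alternative 0.45, 24 patients and power 82.7%.

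**The concern.** The two sides of the comparison appear to count different events. The trial's rate includes near-pCR; the benchmark, as the Background describes it, does not. In any series, pCR plus near-pCR is at least as large as pCR alone. A pCR-only benchmark can therefore equal or understate the matching composite benchmark, but never overstate it, so any error from this source runs towards declaring success.

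This is a single-arm trial, so the fixed null is the only comparator, and the article ties success directly to exceeding single-agent ICI. If part of the margin over 20% comes from adding near-complete responses to one side only, the conclusion that T-VEC improves on single-agent ICI does not follow from a significant test.

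The 20% is also the lower of the two pCR rates cited. The rate cited for nivolumab is 25%, before any near-pCR is added.

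**Working it through.** **Inputs.** From Statistical considerations: n = 24, null 0.20, alternative 0.45, nominal two-sided 10% (5% in the upper tail), stated power 82.7%. From the Background: single-agent pCR rates of 25% (nivolumab) and 20% (pembrolizumab). Not in the article: the single-agent pCR plus near-pCR rate. It is assumed below to be 25% or 30%.

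**Formula.** P(X ≥ r | n, p) = Σ from k = r to n of C(n,k) p^k (1−p)^(n−k).

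**Step 1: the plan's own figure.** The article gives no cut-off, so it is derived. At p = 0.20, P(X ≥ 8) = 0.0892, which exceeds 0.05, and P(X ≥ 9) = 0.0362, which does not. The implied rule is at least 9 of 24 (37.5%). At p = 0.45, P(X ≥ 9) = 0.8270. The stated 82.7% reproduces.

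**Step 2: the same rule when the like-for-like benchmark is higher.** This is the chance of at least 9 of 24 for a regimen whose composite rate only equals that of single-agent ICI.

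| Single-agent pCR + near-pCR | Status | P(X ≥ 9) |
|---|---|---|
| 20% | no near-pCR in the 20% series | 3.6% |
| 25% | assumption | 12.1% |
| 30% | assumption | 27.5% |

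The 25% row is also what results if the nivolumab pCR rate is used as it stands, with no near-pCR added.

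**Step 3: the null reset to a like-for-like rate, n = 24, upper tail at most 5%.**

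| Null | One below the cut-off | Cut-off | Exact error | Power at 45% |
|---|---|---|---|---|
| 20% (as planned) | P(X ≥ 8) = 8.9% | ≥ 9 | 3.6% | 82.7% |
| 25% (assumed) | P(X ≥ 10) = 5.5% | ≥ 11 | 2.1% | 54.6% |
| 30% (assumed) | P(X ≥ 11) = 7.4% | ≥ 12 | 3.1% | 38.5% |

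**Step 4: what a bare success would show.** With 9 of 24 responders the exact (Clopper-Pearson) 90% confidence interval is 21.2% to 56.3%. It excludes 20% but contains both 25% and 30%.

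**Step 5: sample size under a reset null.** For an upper tail of at most 5% and at least 80% power at 45%, the smallest n that first meets both is 36 for a null of 25% (cut-off 14, power 81.7%) and 67 for a null of 30% (cut-off 27, power 81.5%).

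**The case against.** The strongest reply is that the article uses the label pCR loosely. The Abstract attaches that abbreviation to the composite. The Background's aim sentence ends by calling the 45% a pCR rate, although 45% is the composite target. Just after citing 25% and 20%, the Background speaks of improving those pCR or near-pCR rates. So the 20% might already include near-pCR, and only the cited trials could settle it. This stands as a reason for caution. It does not remove the problem: Evaluation of efficacy separates the two categories, the Background labels the cited figures as pCR rates, and the aim sentence names near-pCR on one side of the comparison only. Nowhere does the article say that the 20% includes near-pCR.

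A second reply is that the size of the effect is assumed. That is correct. If the series behind the 20% had no near-complete responses, there is no inflation against that series.

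A reader might infer that the stated error level and power are wrong. The article does not support that. Both are correct for 0.20 against 0.45, and at a true 45% the rule of at least 9 still succeeds 82.7% of the time. The lower powers in Step 3 belong to a different test with a different null.

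A reader might also infer that the primary endpoint should become pCR alone, tested against 20%. That would switch the endpoint with 13 of 24 patients enrolled (Current trial status) and pass over the 25% cited for nivolumab. It would also lose power, because 45% is the expectation for the composite. If near-pCR made up 5 or 10 of those 45 points (assumption), power at a cut-off of 9 would be 67.2% or 47.4%.

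**Conclusion.** The point holds as a mismatch between the endpoint and its benchmark. On the article's own description, 20% is a lower bound for the single-agent pCR plus near-pCR rate. Rejecting it shows a composite rate above 20%; it does not by itself show improvement over single-agent ICI. The direction is known: any error from this source favours success. The size is conditional. False-success probabilities of 12.1% and 27.5% against an intended 5% rest on assumed single-agent composite rates of 25% and 30%, and the article supplies no near-pCR share to choose between them. It matters because the flaw sits in the primary success criterion of a trial with no concurrent control.

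**What to change.** 1. Keep pCR plus near-pCR as the primary endpoint. State whether the 20% includes near-pCR. If it does not, set the null to the pCR plus near-pCR rate of the same single-agent trials.
2. Restate the cut-off, exact error and power for n = 24 under that null, using Step 3 as the pattern.
3. If the composite rate cannot be obtained, report the observed composite with its exact 90% confidence interval and make no claim of superiority over single-agent ICI from the 20% test. Give pCR alone against the cited 20% and 25% as a supportive comparison with its own restated power. With near-pCR assumed to be 5 or 10 of the 45 points, power is 67.2% or 47.4% against 20% (cut-off 9) and 35.0% or 18.3% against 25% (cut-off 11).

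The cost is wording plus a less favourable stated power or a narrower claim. No extra patients are needed if that is accepted; holding 80% power under a reset null would take about 36 or 67 patients.

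The change should be fixed and dated before the response data are analysed. Safety evaluation says that response data are to be kept out of the interim reports. But the trial is open-label and single-centre, with pathology read at the same institute, so investigators may know individual responses. The change should not be described as made without any knowledge of results.
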